#### Procedure

Participants will be recruited using personalized social media messages, targeted social media advertisements, email outreach, flyers within relevant settings, and leveraging the researchers’ professional network. Demographic data as well as their interest in completing in SST training, will be collected through a researcher-developed questionnaire. Participants who show interest in completing the SST training will be randomly allocated to either the intervention group or the control group using the research randomizer software program in 1:1 ratio. The intervention group will have access to the online training program immediately for a period of two weeks. The waitlisted control group will not have access to the online training program during the intervention period, and are offered access after post-test at the end of two weeks.

The pre-test data (T1) is collected using two scales. The first one is a modified version of the BAT-Q Scale [28] with replaced terms like "brief therapy" with "single-session therapy" and "patients" with "clients". These revisions in the item texts of the tool will undergo validation by three psychometric experts. Given that the changes are minor and primarily involve replacing terms to ensure clarity and relevance to the specific context of SST, a consensus among two experts can be considered a reliable validation. The second scale is the counselling self-efficacy scale, COSE-TR [30].

At the end of the two weeks, participants in both the intervention group and the control group will complete a post-test assessment (T2). Participants demonstrating the most significant and least significant changes in attitude and self-efficacy between T1 and T2 will be invited to two separate 30-min focus groups (top 10 and bottom 10, expecting a 50% response rate). This targeted approach facilitates the exploration of contrasting experiences. The SPIRIT Figure in Table 2 explains the schedule of enrolment, interventions, and assessments.

**Table 2 Tab2:** SPIRIT Figure for the Schedule of Enrolment, Interventions, and Assessments

Study period					
	Enrolment	Allocation	Post-allocation		Close-out
Timepoint	T_1_	0	Week 1	Week 2	T_2_
ENROLMENT					
Eligibility screen	X				
Informed consent	X				
Random Allocation		X			
INTERVENTIONS					
SST Training Group			Two weeks access to training		
Waitlist Control Group			No access to training		Two weeks access to training after assessments
ASSESSMENTS					
Quantitative					
BAT-Q	X				X
COSE-TR	X				X
Qualitative					
Selected participants					X

#### Data analysis

Descriptive statistics will be provided for baseline (T1) data. Participant demographics (e.g., age, gender, profession, years of experience, setting) will be described using frequencies and measures of central tendency as appropriate. Internal consistency (e.g., Cronbach's alpha) of both BAT-Q and COSE-TR for Indian population will be evaluated using Jamovi 2.4 software. Missing data will be handled with multiple implementations. Normality of the data will be assessed using the Shapiro–Wilk test.

If the data is found to be normally distributed, independent samples t-test will be used to report the baseline characteristics of the intervention and control groups. ANCOVA will be used to compare the post-intervention outcomes (T2) (self-efficacy, values and attitudes) between the intervention and control groups while statistically controlling for baseline (T1) differences. If the ANCOVA reveals a significant group effect, post-hoc comparisons will be conducted to identify specific differences. Paired samples t-test will be used to analyze changes within each group from pre-test (T1) to post-test (T2) to assess whether there are significant changes over time within each group. If the data is not normally distributed, Templeton’s two-step approach for transformation will be applied. After transformations if the data fails to meet the normality assumption, Mann–Whitney U test will be used to report baseline characteristics. Kruskal–Wallis test can be to identify specific differences between groups. Wilcoxon Signed-Rank Test can be used to assess significant changes over time within each group. All changes will be reported for attitudes, values and four subdomains of self efficacy and p values below 0.05 will be considered significant. Jamovi software will be used for statistical analysis.

To understand the factors influencing the changes observed in the quantitative data, a qualitative analysis will be conducted using six step thematic analysis described Braun and Clarke [38]. Focus group recordings will be transcribed verbatim. The transcripts will be systematically coded, identifying recurring ideas, patterns, and significant quotes related to participants' experiences and explanations for their attitude and self-efficacy changes. Thematic comparisons will be drawn between participants who exhibited significant positive and negative changes in their attitudes, values, and self-efficacy.

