#### Sampling design

Sampling involves purposive sampling for recruitment and then random assigned to experimental and waitlist control groups in 1:1 ratio. To ensure allocation concealment, an independent researcher, unaffiliated with this study, will be responsible for generating the randomization sequence. This researcher will not be involved in participant recruitment, enrollment, or data collection. Randomization can be achieved using the research randomizer software [42]. Participants will be blinded to their group assignment throughout the study. Unblinding will only be permitted under exceptional circumstances and with prior approval from the research ethics committee.

The sample size for this study is determined to be 80 participants, considering an anticipated 25% dropout rate. This decision is informed by the considerations outlined in a similar randomized control trial (RCT) to study the efficacy of a skills training program for 58 mental health support providers by Perlman et al. [43]. The sample size of 60 participants will provide 80% power to detect an effect size of 0.8 [44] between the intervention group and the control group at 5% level of significance (two-tailed test) as evidenced in a similar study by Ho et al. [45] with 68 participants.

To explore contrasting perspectives and for an in-depth understanding of the participant’s experiences, focus groups will be chosen using a targeted homogeneity sampling method, aiming to include those with both the highest and lowest score variances on attitude and self-efficacy scales.

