#### Intervention

The initial training plan outlined in Table 1 will serve as a foundation for the development of the final web-based training program. This plan will undergo rigorous revisions in phases 1 and 2 of the research. The finalized web-based training program is delivered as the intervention to participants in this phase 3 of the research. The final program will consist of both mandatory and optional components. This phase will involve a pre-post test administered to participants who have completed at least the mandatory training hours within a two-week timeframe. To promote adherence to the training time duration, participant progress will be closely monitored, and email reminders will be sent every two days. The waitlisted control group drawn from the same pool as the intervention group, helps mitigate selection bias. Control group will be offered the training program after post-test data is collected from both the groups post two weeks.

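### The missing-data rule may overstate the training effect in all randomised participants if T2 is collected only from those who complete the mandatory training

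*Protocol article*

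**What the plan says.** All references are to Phase 3 of the protocol article.

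- **Data analysis.** The only sentence on missing data is "Missing data will be handled with multiple implementations". It gives no imputation model and no assumption about why data are missing. The between-group comparison is an ANCOVA of T2 adjusted for T1.
- **Sampling design.** Eighty participants are randomised 1:1, "considering an anticipated 25% dropout rate". The dropout figure is not split by arm, and the text does not say whether it means stopping the training or failing to give a T2 score.
- **Intervention.** The section describes a "pre-post test administered to participants who have completed at least the mandatory training hours within a two-week timeframe". It also says that "participant progress will be closely monitored", so some record of training done should exist for each trained participant.
- **Procedure and Table 2.** Participants in both groups are to complete T2 at the end of the two weeks. Table 2 schedules both scales at T2 with no condition on completing the training.

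**The concern.** The Research questions and Expected outcomes sections compare the training group with a waitlist group. A reader of a randomised comparison will take the result as the effect in the groups as randomised.

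Standard multiple imputation assumes that, given T1 and arm, a participant with a missing T2 would have scored like those whose T2 was observed. In the trained arm, under the Intervention wording, every observed T2 comes from someone who finished the mandatory part, and not finishing is itself what makes T2 missing. The imputation then has no data on non-completers and fills their gaps from completers. The waitlist arm has no training to complete before T2, so this filter works in one arm only.

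If non-completers gain less than completers, the estimate drifts towards the effect in those who stayed. The planned output would not show this, because complete-case and imputed results would agree with each other.

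**Working it through.** **The plan's own figure.** Sampling design states "The sample size of 60 participants will provide 80% power to detect an effect size of 0.8". Inflating 60 for 25% dropout gives 60 / (1 − 0.25) = 80, which matches the stated 80 (40 per arm, with 20 losses allowed for in total). For a two-sample t-test, 30 per arm gives about 86% power at 0.8 SD, so 60 is on the safe side. That does not affect this point.

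**Reading the two sections side by side.** In Table 2 the pre-test sits at enrolment, before allocation, so the completion condition in the Intervention section can only act on who gives, or is analysed for, the post-test. Under that section, trained-arm T2 exists only for completers. Under Procedure, it is sought from everyone. The two cannot both govern.

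**Inputs for the illustration.**
- Completer effect: 0.8 SD (the planning effect; treating it as the completer effect is an assumption).
- p, the share of the trained arm missing T2: 0.25 (assumption: the overall allowance falls equally on both arms). Range 0.125 to 0.50; at 0.50 all 20 losses fall among the 40 trained participants.
- e, the gain in trained participants with missing T2: 0, 0.4 or 0.8 SD (assumption; the document gives no figure).
- Waitlist participants with missing T2 do not differ systematically from those observed (assumption; relaxed below).

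**Formulae.** All-randomised effect = (1 − p) × 0.8 + p × e. Imputation at random with arm in the model targets 0.8. Overstatement = 0.8 / (all-randomised effect) − 1.

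For p = 0.25:
- e = 0: 0.75 × 0.8 + 0 = 0.60; 0.8 / 0.60 − 1 = 33%
- e = 0.4: 0.60 + 0.25 × 0.4 = 0.70; 0.8 / 0.70 − 1 = 14%
- e = 0.8: 0.60 + 0.20 = 0.80; overstatement 0

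| p | e = 0 | e = 0.4 | e = 0.8 |
|---|---|---|---|
| 0.125 | 0.70 (14%) | 0.75 (7%) | 0.80 (0) |
| 0.25 | 0.60 (33%) | 0.70 (14%) | 0.80 (0) |
| 0.375 | 0.50 (60%) | 0.65 (23%) | 0.80 (0) |
| 0.50 | 0.40 (100%) | 0.60 (33%) | 0.80 (0) |

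**Simulation check.** 40 per arm, 25% missing in each arm, T1–T2 correlation 0.5 (assumption), 20 imputations, 600 replicates. Mean estimated effect in SD:

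| Scenario | Full data | Imputation with arm | Imputation without arm | Imputed from waitlist | Complete cases |
|---|---|---|---|---|---|
| Missing trained gain nothing | 0.586 | 0.787 | 0.588 | 0.589 | 0.788 |
| Missing trained gain half | 0.700 | 0.805 | 0.603 | 0.602 | 0.803 |
| Missing trained keep full gain | 0.804 | 0.808 | 0.604 | 0.605 | 0.808 |
| Missing trained gain nothing, missing waitlist also 0.8 SD worse | 0.807 | 0.806 | 0.602 | 0.602 | 0.804 |

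The first two rows confirm the algebra and show that imputation with arm removes none of the bias left by complete cases. The last two rows show when there is no bias, and that imputing from the waitlist arm then understates the effect.

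**The case against.** The strongest objection is that the protocol does not state the method being criticised. It does not say imputation alone, imputation within arm, or missing at random, and details of the model and sensitivity analyses are commonly left to a full protocol or SAP that is not shown. This stands in part: the absence of a model or of a sensitivity analysis is not in itself the point. The point is that the stated term is wrong and that the Intervention section sets a completion condition which undermines the natural reading of it.

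A second objection is that stopping the training is not the same as missing T2. Under Procedure, someone who stops but fills in the online form is observed, not imputed. This is correct, and it is why the two sections must be reconciled first.

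A third is that the direction is not fixed. A reader might infer that the effect is certain to be inflated, always in favour of training, by a third. The documents do not support that. The bias is zero if those with missing T2 keep the benefit, or if waitlist losses are equally worse off. If arm is left out of the model and the missing participants keep the benefit, the effect is understated (0.60 against 0.80). The 25% is an overall allowance, not a rate of stopping training in one arm.

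Finally, one might want to require significance in the control-based analysis before benefit is claimed. That is a trade-off, not a necessity: at 0.60 SD an unadjusted two-sided t-test with 30 to 40 per arm has roughly 63% to 75% power, and the analysis is deliberately unfavourable to training. Reporting it beside the main estimate is enough.

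**Conclusion.** The point holds as a conditional one. The missing-data sentence names no recognisable method, and the Intervention and Procedure sections disagree on who takes the post-test. If it means imputation at random with arm in the model, if the completion condition governs, and if non-completers gain less than completers, the effect in all randomised participants is overstated. With the planning effect of 0.8 SD in completers and 25% of the trained arm missing, the size is 0.20 SD (33%) for no gain, 0.10 SD (14%) for half the gain and nothing for the full gain. These gains, and the equal split of losses between arms, are assumptions. If Procedure governs and non-completers do return T2, much of the problem goes away, which is a reason to settle the question before T2 data are collected.

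**What to change.** 1. In Data analysis, correct the term to multiple imputation and state the assumption: missing at random given T1 and arm, with both in the model.
2. Reconcile Intervention with Procedure so that T2 is sought from everyone randomised, whether or not they complete the training.
3. Add the recorded training hours for the trained arm to the imputation model where non-completers have an observed T2. If none do, this cannot help: there would be only completers to learn from.
4. Pre-state one sensitivity analysis that imputes trained-arm non-completers with missing T2 from the waitlist arm. Report it beside the main estimate. If the two differ materially, describe the main result as applying to those who stayed.

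The cost is a change of wording, asking non-completers to fill in the same online form, and one extra analysis run. The downside is a possibly smaller effect in the sensitivity analysis, which will be too low if those with missing T2 in fact kept the benefit.

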## Ethical considerations

The Institution Review Board of the authors’ University has provided ethical clearance (CU: RCEC/00583/02/24) for the research proposal. Throughout the research, adherence to the APA codes of ethics is maintained. Participants are required to provide informed consent, ensuring they have a clear understanding of the purpose, procedures, and their right to withdraw at any time. Voluntary participation is emphasized, with no negative consequences for non-participation or withdrawal. Confidentiality and privacy of participants' personal information is protected through secure data storage and anonymization, with access to the researchers only. Participation in this study is expected to be safe and without any foreseen negative consequences. As such, no specific guidelines for stopping participants early are needed, and no interim analyses are planned. This publication is based on protocol version 1 (02–03-2024). Protocol modifications will be reported in forthcoming publications, if applicable. The research findings will be disseminated through publications in peer-reviewed journals, presentations at relevant research conferences, and other appropriate platforms. Authorship for all publications will follow the Vancouver recommendations for ethical authorship. Recruitment for the study is expected to be completed by February 2025.

## Expected outcomes

The first phase of needs assessment and curriculum development explores the alignment between the proposed SST training curriculum and the perceived training needs of mental health support providers. The findings from this phase will be used to develop a detailed training curriculum that addresses the identified needs. Second phase involves the development and validation of a web-based SST training program to ensure its content validity and alignment with evidence-based practices. It is hypothesised that there will be a high level of agreement among experts on the content validity of each module in the web-based SST training program. The final phase of the study will involve a randomized controlled trial to evaluate the effectiveness of the online SST training program. The hypothesis is that the intervention group will demonstrate significantly greater improvements in attitudes, values, and self-efficacy towards SST compared to the control group. The qualitative data from the FGDs in this phase will explain the factors that influenced their changes.

## Implications of the research

This research offers potential contributions to society, mental health support providers, and research. For the society, SST training for mental health support providers could expand the availability of brief, cost-effective therapy, making it more accessible for individuals who might face limited time or financial resources. By promoting awareness and understanding of SST as a viable option, the research could contribute to destigmatizing mental health interventions and encourage help-seeking behavior.

For mental health support providers, it could enhance the skills and confidence, potentially leading to better client outcomes. Effective SST training could enhance job satisfaction by allowing them to efficiently help more clients and potentially reduce burnout rates in the mental health field. While SST has gained traction and research attention in developed nations like Australia, the United States, the United Kingdom, Canada, and Sweden, its potential impact may be even greater in LMICs. Its inclusion in the spectrum of mental health service delivery options worldwide deserves serious consideration.

For research and academia, the research would contribute valuable data and insights to the growing body of literature on SST, particularly in the context of India and its cultural nuances. The BAT-Q and COSE-TR will be validated with Indian population and will be available for future use by researchers in India. Universities or training institutes can onboard this training program as a certified course. It will inform future research directions like client outcomes, long-term effects, and specific population groups who might benefit the most from single session thinking.

## Limitations

While this research holds promising potential to address the mental health burden in India through SST training, it is important to acknowledge its limitations. Firstly, cultural nuances can be multifaceted, and the initial tailoring might not encompass all regional sensitivities requiring ongoing refinement. Secondly, relying solely on self-reported measures of attitude and self-efficacy carries the risk of bias. The participants may also vary in their initial training, experience, and exposure. Thirdly, the focus is on immediate changes in attitudes and beliefs, short term or long term follow ups might be beneficial. Finally, the web-based format, though accessible, might exclude individuals with limited internet access or technological literacy. Future research could explore long-term program effects, address access barriers, and incorporate extensive qualitative methods for deeper understanding.

## Data Availability

The training program proposed in this study is adapted from the training and implementation plan described by The Bouverie Centre, La Trobe University, Australia available at https://doi.org/10.1002/anzf.1426 and described in the manuscript. No datasets were generated or analysed during the current study.
